### Statistical analysis

2.8

Statistical analyses will be performed using SPSS software (Version 27.0, IBM Corp.), with a two-tailed *p*-value <0.05 being considered statistically significant. Normally distributed continuous variables will be expressed as mean ± standard deviation, with between-group comparisons being analyzed by independent samples t-test or one-way ANOVA (as appropriate), and within-group comparisons by paired t-test or repeated measures ANOVA. Non-normally distributed data will be presented as median (interquartile range) and analyzed using Wilcoxon rank-sum test. Categorical variables will be reported as frequencies (percentages), with between-group differences being assessed by chi-square test. In clinical between-group multiple comparisons, all *p*-values will be adjusted using the false discovery rate (FDR, Benjamini-Hochberg procedure) to control the risk of false-positive results (11).

Neuroimaging data will be processed using the DPABI V5.4 toolkit. Voxel-based morphometry (VBM) will be implemented to quantify volumetric characteristics of hippocampal subfields, while dynamic functional connectivity (aDC) analysis will be employed to characterize time-varying functional interactions between hippocampal subregions and other brain areas. Covariates including gender, age, educational attainment, and total intracranial volume will be regressed out during preprocessing. Statistical parametric maps will undergo Gaussian Random Field (GRF) correction for multiple comparisons at the cluster level. To detect voxel-wise alterations in hippocampal subfield functional connectivity (FC), mixed-effects models will be constructed to assess group differences, with interaction effects rigorously tested through permutation testing. All statistical outcomes will subsequently undergo False Discovery Rate (FDR) correction to control family-wise error across the entire analytical pipeline.

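### Section 2.8 says FDR correction controls family-wise error across the whole pipeline; FDR does not do this once some effects are real, so the imaging findings would carry the wrong error-rate label

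*Protocol article*

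**What the plan says.** All the relevant text is in the protocol article, section 2.8 Statistical analysis.

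- General significance level: "with a two-tailed *p*-value <0.05 being considered statistically significant". This is the only numeric error level given.
- Clinical between-group comparisons: "all *p*-values will be adjusted using the false discovery rate (FDR, Benjamini-Hochberg procedure) to control the risk of false-positive results". This names the procedure and makes no family-wise claim.
- Imaging maps: "Statistical parametric maps will undergo Gaussian Random Field (GRF) correction for multiple comparisons at the cluster level".
- Voxel-wise connectivity: "mixed-effects models will be constructed to assess group differences, with interaction effects rigorously tested through permutation testing".
- Closing sentence on error control: "All statistical outcomes will subsequently undergo False Discovery Rate (FDR) correction to control family-wise error across the entire analytical pipeline".

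The imaging work covers at least two metrics, hippocampal subfield volume by VBM and dynamic connectivity of hippocampal subregions. The number of subregions, contrasts and maps is not stated. Nothing elsewhere in the article qualifies the closing sentence.

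**The concern.** False discovery rate and family-wise error rate are different quantities. FDR is the expected proportion of false positives among the rejections; family-wise error is the probability of one or more false positives. They coincide when every null is true. Once some effects are real, each true rejection relaxes the Benjamini-Hochberg threshold for the remaining tests, and the probability of at least one false rejection can climb well above the nominal level while FDR stays below it.

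The trial does not expect every null to be true. The Introduction hypothesises that acupuncture remodels hippocampal subregional connectivity and volume, and the Discussion plans to identify pathological differences between aMCI patients and healthy people. Under those hypotheses the property claimed in section 2.8 does not follow from the method named. A reader of the results would believe that each reported subregion had family-wise protection, when it had the weaker FDR protection.

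**Working it through.** **Inputs.** From section 2.8: two-sided 0.05; Benjamini-Hochberg (BH), named there for the clinical comparisons. Assumed: BH at q = 0.05 for imaging too, independent tests, and the test counts below. The article gives no imaging error figure to reproduce beyond the general 0.05.

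**Step 1: all nulls true.** BH at 5% then has a family-wise error of 5%. Simulation (40,000 runs; 10, 20 and 100 tests) gave 0.049 to 0.051. This is the case in which the claim is right.

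**Step 2: some effects real and strong.** Let m be the number of tests and m1 the number of real effects, all certain to be rejected. A null is then rejected if the smallest null p-value is at most q(m1 + 1)/m. Ignoring later BH steps, which add little here,

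FWER ≈ 1 − [1 − q(m1 + 1)/m]^(m − m1).

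- 6 tests, 3 real: threshold 0.05 × 4/6 = 0.0333; FWER ≈ 1 − 0.9667³ = 0.097. Simulated (20,000 runs): 0.096.
- 20 tests, 10 real: threshold 0.05 × 11/20 = 0.0275; FWER ≈ 1 − 0.9725¹⁰ = 0.243. Simulated: 0.241.

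**Step 3: less extreme effects.** With 20 tests and 10 real effects (40,000 runs), family-wise error was 0.197 at a mean z of 3 and 0.244 at a mean z of 5. FDR was 0.025 in both, as expected from q × (m − m1)/m = 0.05 × 10/20. With 10 tests and 2, 5 or 8 real effects, family-wise error ran from 0.076 to 0.139. So BH delivers FDR control and not family-wise control.

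**Step 4: Holm on the same tests.** Holm kept family-wise error between 0.014 and 0.050 across all simulated scenarios.

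**Step 5: does the across-map step after GRF help or harm?** Treat each map as giving one p-value already corrected within the map, with half the maps carrying a real effect.

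| Maps | GRF within map only | GRF, then BH over all maps | GRF, then BH over surviving maps only |
|---|---|---|---|
| 6 | 0.139 | 0.093 | 0.139 |
| 12 | 0.265 | 0.159 | 0.265 |
| 24 | 0.463 | 0.272 | 0.463 |

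The first column is close to 1 − 0.95^k for k null maps; for 12 maps, 1 − 0.95⁶ = 0.265. The last column equals the first because every survivor already has p ≤ 0.05, so BH at 5% rejects them all. BH over all maps lowers the family-wise error, although not to 0.05.

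**The case against.** The best defence is that only a label is wrong. FDR is a legitimate target for mechanistic imaging, imaging is secondary to the AVLT-H, and the clinical comparisons use FDR without a family-wise claim. That stands, and it is why rewording alone is sufficient.

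The sizes are also fairly challenged. The test counts are assumed, neighbouring subregions are unlikely to be independent, and certain rejection of the real effects is a limiting case. If the null tests were perfectly correlated, or only one null were true, BH would hold family-wise error at 5%. This limits the figures; it does not turn FDR control into family-wise control.

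Several stronger readings are tempting and are not supported:

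- *Multiplicity across subregions and metrics is uncontrolled.* The closing sentence covers all outcomes, so on its face that multiplicity is FDR-controlled under the wrong name.
- *Three corrections are stacked in series.* Permutation is described as the way interaction effects are tested ("with interaction effects rigorously tested through permutation testing"). It is not called a multiplicity correction, and the text does not say that GRF is applied to the same maps.
- *FDR is run on thresholded maps, where no p-values are defined.* The text does not say so. Map-, cluster- or region-level p-values would be well defined, and a condensed article may leave the unit and level to the full plan.
- *The FDR step after GRF should go.* Step 5 shows that dropping it without a replacement raises family-wise error.
- *A stated numeric imaging error rate is wrong.* None is stated.

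**Conclusion.** The concern holds as a misstatement of which error rate is controlled. Section 2.8 attributes family-wise control to FDR, and that fails in general once real effects and several true nulls are mixed, which is what the trial's own hypothesis implies. For scale, family-wise error is about 10% (6 tests, 3 strong effects) and about 24% (20 tests, 10 strong effects), assuming independence and BH at 5%. The counts are illustrative because the article gives none.

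The consequence falls mainly on the secondary imaging claims. A reader might infer that the primary AVLT-H result is compromised too. That would require taking the closing sentence, which ends the imaging paragraph, to override the separate and correctly worded clinical provision, and the text does not establish this.

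**What to change.** Choose one of two changes to the closing sentence of section 2.8.

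1. Replace *family-wise error* with *false discovery rate*, and report the imaging findings as FDR-controlled. This costs a few words and leaves the planned procedure as it is.
2. If family-wise control is wanted, list the subregions and metrics in advance and use Holm, or max-statistic permutation, across that list. The cost is a stricter threshold. With 6 tests and 3 already rejected, the next p-value must be at most 0.05/3 = 0.0167 under Holm, against 0.0333 under BH. With 20 tests and 10 rejected, it is 0.05/10 = 0.005 against 0.0275.

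Under either option, keep GRF as the within-map correction and apply the across-map step to the p-values of all maps, including those that do not survive GRF. Do not remove the across-map FDR step unless a family-wise procedure takes its place. Settle the choice before the imaging data are analysed.

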### Safety measurements

2.9

Any possible accidental injuries caused by this study will be prevented as much as possible, the relevant medical expenses will be covered by the research project team, and the participants will receive certain financial compensation. Any unexpected adverse events during the intervention period will be monitored and reported to a research assistant. Causality in relation to the acupuncture intervention and the severity of adverse events will be analyzed. Serious adverse events will be reported to the ethics committee.

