Recently, acupuncture, as a safe and reliable non-drug therapy, has been fully confirmed for its efficacy in the treatment of cognitive impairment (10–14). Our previous randomized controlled trial (RCT) also proved it can alleviate cognitive symptoms (15). However, the mechanism of acupuncture treating aMCI has not been revealed.

With the development of magnetic resonance imaging (MRI) technology, several studies have shown that the structure and function of specific brain regions are altered in patients with aMCI (16–18). Notably, the hippocampus, as the hub of regions dealing with episodic memory (19), is closely related to the development of aMCI (20). Episodic memory is a declarative memory in which the brain combines the content of an event that triggers an individual’s emotional or ideological awakening with spatio-temporal information to encode and store it (21). Episodic memory belongs to the category of long-term memory, which is an advanced cognitive function possessed by humans. The researchers found that during the formation, object “what,” spatial “where” and temporal “when” of episodic memory were transmitted to the hippocampus through different information flow paths for integrated coding (22) Researchers found that there is a decrease in the volume of the hippocampus and abnormal hippocampal dynamic functional connectivity (dFC) in aMCI, compared to healthy people (23, 24).

Therefore, we hypothesize that acupuncture could enhance episodic memory in aMCI by remodeling hippocampal subregional connectivity and volume, thereby offering a mechanistic basis for its clinical application. Then we designed a randomized controlled trial with the aim of (1) evaluating the efficacy and safety of acupuncture in improving episodic memory in aMCI patients and (2) exploring the structural and functional changes of hippocampal subregion underlying acupuncture’s therapeutic effects.

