### Study design

2.1

This is a prospective, single-center, three-armed, parallel-designed, assessor-blinded, randomized controlled trial. A total of 150 participants with aMCI and 50 healthy controls (HCs) will be enrolled. The 150 eligible patients will be randomly assigned to the verum acupuncture group, the sham acupuncture group, and the waiting group in a ratio of 1:1:1. Healthy volunteers will serve as a comparison group for baseline comparisons. The enrollment schedules, interventions, and assessments are summarized in Table 1. A study flowchart is provided in Figure 1.

**Table 1 tab1:** Schedule of enrollment, intervention, and assessments.

Item	Study period				
	aMCI				Healthy volunteers
	Baseline	Treatment phase			Baseline
	0 week	Week 1	→	Week 12	0 week
Enrollment					
Inclusion criteria	×				×
Exclusion criteria	×				×
Informed consent	×				×
Intervention					
Verum acupuncture group		×	×	×	
Sham acupuncture group		×	×	×	
Control group					
Outcome measurement					
Clinical features					
AVLT-H	×			×	×
MoCA	×			×	×
MMSE	×			×	×
HAMD-17	×			×	×
fMRI					
3DT1WI	×			×	×
T2WI	×			×	×
Flair	×			×	×
rs-fMRI	×			×	×
DTI	×			×	×
Safety					
Adverse events		×	×	×	

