#### Waiting group

2.6.3

Patients in the WG will not receive acupuncture treatment during the observation period, and they will be provided 36 acupuncture sessions for free after observation.

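### Section 2.9 words adverse-event monitoring as covering unexpected events, which is narrower than Table 1, the planned causality and severity analysis, and the safety aim

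*Protocol article*

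**What the plan says.** The Introduction of the protocol article gives the first aim as "evaluating the efficacy and safety of acupuncture in improving episodic memory in aMCI patients", so safety is a stated objective.

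Section 2.9 (Safety measurements) has one sentence on what is collected: "Any unexpected adverse events during the intervention period will be monitored and reported to a research assistant". It continues: "Causality in relation to the acupuncture intervention and the severity of adverse events will be analyzed". It then adds: "Serious adverse events will be reported to the ethics committee". Neither of these two later sentences is limited by expectedness.

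Table 1 in section 2.1 (Study design) has a row under Safety labelled "Adverse events". It is marked from week 1 to week 12 under the aMCI heading, again without a qualifier.

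Section 2.8 (Statistical analysis) has a general rule that could serve for adverse-event counts: "Categorical variables will be reported as frequencies (percentages), with between-group differences being assessed by chi-square test".

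**The concern.** The adjective *unexpected* in the collection sentence works as a filter. In a trial of needling, the reactions most plausibly caused by the treatment are also the most foreseeable, and read literally they fall outside what section 2.9 says will be monitored. The other places that deal with adverse events do not apply the filter, so site staff have two scopes to choose from.

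At stake is the comparison of harms between arms. Verum is the only arm in which needles pass through the skin before week 12. Sham uses a blunt, non-penetrating needle (section 2.6.2), and the waiting group receives no needling in that period (section 2.6.3). A filter on foreseeable reactions would therefore remove events mainly from one arm. Events that were never recorded cannot be restored at the analysis stage.

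**Working it through.** The plan gives no figure on this point and no event rate, so there is nothing to reproduce. The check is a comparison of the passages, followed by a short piece of algebra on direction.

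**1. Scope of adverse events, place by place**

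- Introduction, aim 1: safety of acupuncture, no limit.
- Section 2.1, Table 1: adverse events in weeks 1 to 12, no limit by expectedness.
- Section 2.9, collection sentence: unexpected events, during the intervention period.
- Section 2.9, analysis sentence: causality and severity of adverse events, no limit.
- Section 2.9, serious events: no limit.

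The narrow wording stands in one place, but that place is the sentence on collection. Table 1 fixes when events are noted and does not define an event. The analysis sentence can work only on what has been collected. So either section 2.9 restricts collection, or it contradicts Table 1. Both readings call for a correction.

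**2. Can the filter be applied consistently?**

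The article neither defines *unexpected* nor lists expected reactions. It does describe sensations that it anticipates: section 2.6.1 seeks De qi, which includes soreness and numbness, and section 2.6.2 says that the sham needle feels like a pinprick. A practitioner could regard a complaint of soreness as expected and not pass it on. Section 2.5 says that participants, acupuncturists and intervention supervisors are not blinded, so this judgement may differ between arms.

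**3. Which arms and which weeks?**

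Section 2.9 refers to an intervention period. For the waiting group, section 2.6.3 speaks only of an observation period. Table 1 suggests that weeks 1 to 12 apply to every aMCI patient, but section 2.9 does not say so.

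**4. Direction of the possible bias**

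Let u be the proportion of patients in an arm with at least one unexpected event, and f the proportion with foreseeable reactions only. V denotes verum and S sham.

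- Difference with all events recorded: (u_V + f_V) − (u_S + f_S).
- Difference under the literal rule: u_V − u_S.
- Amount lost: f_V − f_S.

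The loss is zero only if f_V = f_S. If f_V exceeds f_S, which is an assumption based on skin penetration in verum alone, the recorded difference understates the excess in verum. Where unexpected events are about equally common in the two arms, it shrinks towards zero. The same holds with the waiting group in place of sham. The documents give none of the four quantities, so no size can be put on it. The chi-square comparison in section 2.8 sees only recorded events and cannot correct the loss.

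**The case against.** The case against is substantial. Section 2.9 does not say that *only* unexpected events are monitored. With no list of expected reactions, staff would have nothing against which to apply such a filter, and the word may be a loose choice for *untoward*. A plan to assess causality in relation to acupuncture also fits poorly with discarding the reactions most likely to be caused by it. Definitions and collection procedures may sit in the full protocol, which is not shown.

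Most of this stands as a limit on how far the point can go. It is not established that known reactions will go uncounted. But the objection does not remove the inconsistency: the restriction is stated text, not a detail left to another document, and a charitable reading by a reviewer does not bind the staff who record events.

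Three stronger inferences are tempting, and the documents do not support them.

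- A reader might conclude that the safety aim cannot be answered. Even on the strictest reading, unexpected events are collected and serious events are reported, so the assessment would be incomplete, not impossible.
- A reader might take the volume of treatment, 50 patients × 36 sessions = 1,800 verum sessions, as the size of the problem. That is exposure at full attendance. It says nothing about how many events would be missed.
- A reader might count the waiting group's later treatment as a gap, since "they will be provided 36 acupuncture sessions for free after observation". Those sessions fall after the randomised comparison and cannot bias it, and a collection window ending at week 12 agrees with Table 1.

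**Conclusion.** The point holds as an inconsistency in a stated rule. The collection sentence in section 2.9 is narrower than Table 1, the analysis sentence that follows it, and the safety aim. If it is followed literally, the between-arm safety comparison would be incomplete and could be biased towards no difference.

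The bias is conditional on two assumptions: that staff apply *unexpected* as a filter, and that foreseeable reactions are more common in verum than in the other arms. The article confirms neither, and the size is unknown. The point is modest in weight, but it merits correction because unrecorded events cannot be recovered once data collection is over.

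**What to change.** Delete *unexpected* from the collection sentence in section 2.9 and bring the sentence into line with Table 1. Suggested wording: *All adverse events, expected or not, will be recorded in the same way in all three randomised groups from week 1 to week 12 and reported by group.* Naming the weeks also removes the doubt about what the intervention period means for the waiting group.

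The change is one of wording and leaves the interventions, the visit schedule and the analysis methods as they are. The downside is small: more minor events to log.

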## Discussion

3

The present study suggests that acupuncture improves episodic memory function in aMCI by remodeling the structure and function of hippocampal subregions, which is consistent with the findings of previous studies (11).

In the theory of Traditional Chinese Medicine (TCM), Amnestic Mild Cognitive Impairment (aMCI) is categorized under the condition of “forgetfulness.” The etiology of this disorder is attributed to the deficiency of cerebral essence, the lack of nourishment to the primal spirit, stagnation of qi and dampness, and the failure of clear yang to ascend, which collectively lead to progressive memory loss. Based on clinical experience and previous experimental evidence, the acupuncture prescription has been formulated to address these issues. The prescription includes the following acupoints: Baihui (GV20), Sishencong (EX-HN1), Shenting (GV24), Yintang (EX-HN3), Qihai (CV6), Guanyuan (CV4), bilateral Hegu (LI4), Shenmen (HT7), Zusanli (ST36), Fenglong (ST40), Xuanzhong (GB39), Taixi (KI3), and Taichong (LR3). This selection of acupoints aims to replenish the cerebral essence, nourish the primal spirit, regulate the flow of qi, resolve phlegm, and thereby enhance cognitive function. Moreover, patients with MCI who received acupuncture at acupoints similar to those used in our study (Sishencong EX-HN1, Yintang GV29, Neiguan PC6, Taixi KI3, Fenglong ST40, and Taichong LR3) exhibited improved cognitive function (32). Corresponding rs-fMRI findings demonstrated strengthened functional connectivity within a cognition-associated network post-intervention, specifically within key regions such as the insula, dorsolateral prefrontal cortex, hippocampus, thalamus, inferior parietal lobule, and anterior cingulate cortex (32). In addition, acupuncture at Taichong (LR3) and Hegu (LI4) has been shown to activate prefrontal and hippocampal regions – critical hubs for memory consolidation – in both MCI and Alzheimer’s disease populations (33).

The hippocampus, as an important brain region in the central nervous system, is involved in learning and memory storage (34). However, it is recognized that the cytoarchitecture of hippocampus is not homogeneous (35). A growing body of research has found that analyzing of hippocampal subregions better detects subtle changes in hippocampal structure, more accurately discerns the cognitive relevance of these changes (36, 37). Therefore, it is necessary and reasonable to explore acupunctures based on hippocampal subregions to improve episodic memory functions. Modern studies have demonstrated that acupoints such as Baihui (GV20), Shenting (GV24) and Sishencong (EX-HN1) can improve cognitive function (38–40), which aligns with the traditional TCM theory of nourishing the brain and enhancing memory. Animal experiments further confirm that electroacupuncture at Baihui (GV20) and Shenting (GV24) can affect proteomic changes in the hippocampus of rats with cognitive impairment, increase the basic synaptic transmission efficiency and synaptic plasticity of the hippocampal CA3-CA1 circuit, thereby improving learning and memory ability (38, 39). Through this tailored acupuncture approach integrating classical theory with contemporary neuroimaging evidence, further exploration of the neural mechanisms of acupuncture on episodic memory in aMCI subregions in humans is necessary.

Furthermore, in the design of using sham acupuncture as the control group, we will use blunt needles at acupoints rather than non-acupoints. The primary reason is that this study aims to verify the therapeutic mechanism of acupuncture on episodic memory in aMCI patients, not to validate acupoint specificity. Applying blunt needles at acupoints for SA aims to maximally simulate the VA treatment environment (including the operation site, doctor-patient interaction, and sensory experience), thereby more strictly controlling the placebo effect and reducing the risk of unblinding for patients. In fact, regarding acupoint selection, in addition to the 362 conventional acupoints, there are numerous extraordinary acupoints distributed throughout the body. Therefore, it is difficult to find inactive superficial acupoints. Concerning needle insertion methods, both superficial needling and needle withdrawal create some nerve stimulation in the area. This stimulation can then affect related parts of the brain, leading to what are called “edge contact effects,” which is not an inactive placebo (41, 42). Therefore, this finding does not mean that acupoints are unimportant, it shows that the we must carefully consider the placebo effect in acupuncture research.

The main advantages of this study are as follows: first, aMCI patients will be compared with healthy individuals to identify pathological changes in hippocampal subregions. Meanwhile, we will explore how acupuncture reverses hippocampal neuroplasticity alterations in aMCI. The mechanism of acupuncture’s efficacy is based on a rigorous experimental design, ensuring the reliability of the results.

The limitations of this study include the potential difficulty in implementing blinding for sham acupuncture. Additionally, due to the large number of acupuncture points used, it is challenging to identify the specific mechanisms of individual points. Moreover, given the long treatment course, there will be a considerable risk of patient dropout before completing the entire course.

In conclusion, the efficacy of acupuncture in improving episodic memory in patients with amnestic mild cognitive impairment (aMCI) will be further confirmed. This improvement will be achieved by modulating the structural and functional connectivity of hippocampal subregions, leading to enhanced episodic memory function. We hope this can provide an alternative treatment option for aMCI, laying the foundation for personalized precision treatment and outcome prediction.

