**Methods:**

A randomized, controlled, blinded research will be performed. 150 aMCI participants will be assigned to the verum acupuncture group, sham acupuncture group, and waiting group; 50 healthy controls will also be recruited. Patients in the acupuncture group will receive real acupuncture treatment or placebo acupuncture three times per week, 36 sessions over 12 consecutive weeks in total. Patients in the waiting group will receive the same verum acupuncture treatment for compensation after the trials are finished. The primary outcome will be the auditory-verbal learning test. Secondary outcomes will include Montreal Cognitive Assessment (MoCA), Mini-Mental State Examination (MMSE), Hamilton Depression Scale (HAMD), and functional magnetic resonance imaging data. Outcomes will be measured at baseline and 12 weeks after randomization. Repeated measurement analysis of variance will be used to explore the intervention effect.

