### Sample size

2.2

The sample size for MRI studies is typically determined by practical constraints such as scanning time, cost, and effect size, so there is no unified standard. Desmond et al. conducted a statistical efficiency analysis based on the estimation of sample size in MRI studies, indicating that approximately 12 participants can achieve 80% power in typical activation at the voxel level (25). After considering that increasing the sample size could significantly enhance the stability of the results and accounting for a certain dropout rate, we therefore decided that each group will include 50 participants, totaling 150 aMCI patients and 50 healthy controls.

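### Course-related dropout, a final visit tied to the last needling session and tests that need a final value together risk comparing mainly course completers with nearly the whole waiting arm

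*Protocol article*

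**What the plan says.** **Expected loss.** The limitations paragraph of the Discussion states that "given the long treatment course, there will be a considerable risk of patient dropout before completing the entire course". Section 2.2 fixes the group size after "accounting for a certain dropout rate", without giving the rate.

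**Who has a course.** The Abstract sets 36 sessions over 12 weeks for the needling arms. Under 2.6.3, "Patients in the WG will not receive acupuncture treatment during the observation period"; these patients are offered 36 free sessions afterwards.

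**When the final assessment falls.** The Abstract puts it 12 weeks after randomisation, and Table 1 puts it at week 12. Sections 2.7 (scales) and 2.7.3 (MRI) put it 24–72 h after the last acupuncture, for all patients.

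**How clinical outcomes are analysed.** The Abstract says: "Repeated measurement analysis of variance will be used to explore the intervention effect". Section 2.8 names the independent t-test or one-way ANOVA between groups, "within-group comparisons by paired t-test or repeated measures ANOVA", and a Wilcoxon rank-sum test for non-normal data. P-values in clinical between-group multiple comparisons are FDR-adjusted. Mixed-effects models are named only for functional connectivity.

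**The concern.** Each passage is unremarkable alone; the problem lies in how they combine. The authors expect a considerable number of patients not to finish, and they give the length of the course as the reason. That reason exists in two of the three arms. Waiting patients have no course to abandon, and the promised free sessions give them some reason to stay.

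The session-based timing adds to this. A patient who stops in week 5 is due for the final scales and scan in week 5, or has no usable final visit. In the first case a week-5 value stands beside week-12 values. In the second case the patient drops out of every named clinical test, unless values are imputed.

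If those who stop are on average those who feel no benefit, have discomfort or are declining, removing them raises the mean change in the needling arms and leaves the waiting arm as it was. Verum could then appear better than waiting with no true effect, which bears directly on the first aim, efficacy on episodic memory. Enrolling more patients restores precision but does not remove the selection.

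**Working it through.** **1. The plan's own figure.** Section 2.2 starts from the statement that "approximately 12 participants can achieve 80% power in typical activation at the voxel level" and arrives at 50 per group. Inflating 12 for dropout gives 12/(1 − 0.10) = 13.3, so 14, and 12/(1 − 0.40) = 20. Reaching 50 by dropout alone would need 1 − 12/50 = 76%. Section 2.2 also cites stability of results, so 50 is a judgement from which no dropout rate can be recovered. The 50 is not disputed here, but any dropout rate used below has to be an assumption.

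**2. The two timings side by side.**

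| Patient | Abstract and Table 1 | Sections 2.7 and 2.7.3 |
|---|---|---|
| Completes 36 sessions | week 12 | 24–72 h after session 36, about week 12 |
| Stops in week 5 | week 12 | about week 5, or not defined |
| Waiting arm | week 12 | no last acupuncture during observation |

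The two agree only for completers.

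**3. What the named tests need.** The paired t-test and repeated-measures ANOVA need both values. The between-group tests on the final value or on change need the final one. Every patient is evaluated at baseline before randomisation (2.5), so without imputation all of them use the same set: patients with a final value.

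**4. Size of the possible bias.** From the document: 50 per arm and two-sided 5%. Assumed: no true effect; a share d lost under verum; none lost in the waiting arm; staying determined by a latent normal tendency correlated r with AVLT-H change; within-arm SD of 1, ignoring the small variance reduction from selection.

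- Bias in SD = r × φ(z)/(1 − d), with z = Φ⁻¹(1 − d).
- d = 0.2: φ(0.842)/0.8 = 0.280/0.8 = 0.350.
- d = 0.3: φ(0.524)/0.7 = 0.348/0.7 = 0.497.
- SE = √(1/[50(1 − d)] + 1/50). For d = 0.2, √(1/40 + 1/50) = 0.212. For d = 0.3, √(1/35 + 1/50) = 0.220.
- Rejection rate = P(|Z + bias/SE| > 1.96).

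| d | r | Bias (SD) | Rejection rate, unadjusted 5% test |
|---|---|---|---|
| 0.2 | 0.2 | 0.070 | 6.3% |
| 0.2 | 0.3 | 0.105 | 7.8% |
| 0.2 | 0.5 | 0.175 | 13.1% |
| 0.3 | 0.2 | 0.099 | 7.4% |
| 0.3 | 0.3 | 0.149 | 10.4% |
| 0.3 | 0.5 | 0.248 | 20.3% |

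**5. Check with a different parameterisation.** Let completers do g SD better than stoppers. The bias is then d × g.

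- d = 0.1, g = 0.25: bias 0.025 SD, rejection 5.2%.
- d = 0.2, g = 0.5: bias 0.10 SD, rejection 7.6%.
- d = 0.3, g = 0.75: bias 0.225 SD, rejection 17.5%.

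The order of magnitude is the same.

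**The case against.** A reader might infer that the plan treats stopping the course as leaving the trial and restricts the analysis to completers. The article does not say so. The sentence on dropout is a prediction among the limitations and sets no withdrawal rule. Section 2.7 says that all patients are assessed twice, and the Abstract and Table 1 allow a patient who stopped in week 5 to be seen at week 12. Analysis sets and missing-data handling may be in a full protocol or SAP that is not shown. Their absence is no finding, and imputation cannot be ruled out. All of this stands, and it limits the point to a risk arising from the stated passages.

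The figures are also open to challenge, with good reason. Dropout rate, correlation and zero waiting-arm loss are all assumed, and the last of these maximises the imbalance. Patients who feel better may also stop, which would weaken or reverse the bias. The rejection rates ignore the FDR adjustment in 2.8, so they are not error rates of the plan as written.

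Two further inferences go too far. Verum and sham share the same 36 sessions, so that contrast is affected only if stopping differs between real and placebo needles. And although mixed models are named for connectivity, the article does not say that patients with only a baseline scan are kept, so it does not follow that the imaging and memory results rest on different patients.

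What the objection leaves untouched is the conflict in timing, the lack of a meaning for the session-based visit in the waiting arm, and the choice of tests that need a final value when considerable course-related loss is expected.

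**Conclusion.** The point holds as a risk, mainly for the verum–waiting and sham–waiting comparisons. It rests on stated text: the expected course-related dropout, a course that only the needling arms have, two incompatible timings for the final assessment, and clinical tests that without imputation use only patients with a final value.

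Under the assumptions above, a spurious benefit of 0.07–0.25 SD is possible. It is at the low end if stopping is only weakly related to memory change, and smaller still if the waiting arm also loses patients. These figures illustrate the scale and do not predict this trial's result. The change is worth making because it is cheap and because the timing passages have to be reconciled in any case.

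**What to change.** - **Sections 2.7 and 2.7.3:** reconcile them with the Abstract and Table 1. Invite every randomised patient, in all three arms, to the AVLT-H, MoCA, MMSE, HAMD and MRI visit 12 weeks after randomisation whatever number of sessions was attended, unless consent to follow-up is withdrawn.
- **Section 2.8 and Abstract:** analyse AVLT-H by assigned arm with a likelihood-based mixed model (arm by time, baseline and week 12) in place of repeated-measures ANOVA.
- **Sensitivity:** add one analysis that gives missing needling-arm values a less favourable, missing-not-at-random assumption.

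The order of importance matters. The mixed model is valid under missing at random. In the scenario computed above, loss depends on the unobserved change itself, so the model alone would not remove that bias. Following up those who stop is what mainly does so, and the sensitivity analysis covers what is still missing.

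The cost is some rewording, contacting patients who stop for a visit already scheduled, and a little more analysis work. The estimated effect may turn out smaller. No extra patients or procedures are needed.
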